#### Criterion of secondary therapeutic evaluation index/criterion of secondary therapeutic outcomes

5.2.2

1.Activity of daily living (ADL) scales (modified Barthel index); WAB; water swallow test; MoCA; GAP-43; MAP-2.2.The quantified and classified standard for TCM symptoms*Effectivity*: the symptoms and signs in TCM improve and the score n ≥ 50%;*Inefficiency*: the symptoms and signs in TCM do not obviously improve, or even become worse, and the score n < 50%.n = [(total score before treatment − total score after treatment) ÷ total score before treatment] × 100%.3.The comparison of obvious effective rate and effective rate among groups and within groups made by ADL scales (modified Barthel index), WAB and water swallow test; the comparison of before-and-after treatment in GAP-43 and MAP-2.

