### Enrollment and recruitment of participants

3.1

1.Enrollment: subjects of the study will be recruited through television, radios, newspapers, communities, and hospitals on the principle of respecting subjects’ privacy and voluntary participation.2.Inclusion criteria: researchers in each subcenter are responsible to introduce the objectives, design, process, benefits, risks, and compensation in this study to subjects. According to the diagnostic criteria, inclusion criteria and exclusion criteria, researchers conduct preliminary screening for the recruited subjects. Those who meet the criteria are subjects who may participate in the study. They will sign the informed consent and their name, gender, age, address, telephone number, and other information should be recorded in detail.3.Screening: subjects who may participate in the study are further screened according to the diagnostic criteria, inclusion criteria, and exclusion criteria. Those who have met the criteria and signed the informed consent will conduct the basic questionnaire survey within 14 days before the treatment period. Subjects who can complete the questionnaire under guidance (more than 80% completion without logical problem) will be screened by physical and chemical examination indicators. The qualified ones will participate in clinical trials.

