### Inclusion criteria

3.3

Age 30 to 75 years;Meet the diagnostic criteria for cerebral infarction and intracerebral hemorrhage;Meet the diagnostic criteria for stroke and staging criterion in traditional Chinese medicine,The onset time of cerebral infarction or intracerebral hemorrhage is within 3 months; the evaluation of modified Barthel index is less than 70 points, and the evaluation of modified Rankin scale is more than 3 points;Modified Barthel index < 70, MRS ≥ 3;Patients and his family members both voluntarily agree to participate in this clinical trial and sign the informed consent.

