1.*Eye-acupuncture physical therapy*: Eye-acupuncture physical therapy includes eye-acupuncture exercise therapy and eye-acupuncture equipment training. Needles are embedded in the liver region, kidney region, upper-jiao region, and lower-jiao region on both sides. The rehabilitation programs are determined by functional evaluation. Participants are expected to recover or improve dysfunction by taking various kinds of exercise training with hands or equipment, which include limb intelligent feedback training system, gait analysis treadmill, intelligent sports training device, electric erecting bed training, dysphagia therapeutic apparatus, scene interactive rehabilitation system, balance function examination training system, and so on.2.*Eye-acupuncture occupational therapy*: Needles are embedded in the liver region, kidney region, upper-jiao region, and lower-jiao region on both sides of the eyes. At the same time, participants get training and treatment by choosing purposeful activities based on their needs in daily life, family life, social intercourse, and career.3.*Eye-acupuncture speech training*: Needles are embedded in the upper-jiao region, lower-jiao region, heart region, and spleen region on both sides of the eyes for participants with speech disorder. At the same time, conducting the conventional speech training4.*Eye-acupuncture cognitive rehabilitation training*: Needles are embedded in the upper-jiao region, lower-jiao region, heart region, and kidney region on both sides of the eyes. At the same time, rehabilitation treatment for attention, memory, calculation, thinking, the ability to solve problems and execute, and perceptual disorder is implemented in order to improve cognitive function and activity of daily living.5.*Eye-acupuncture pain rehabilitation techniques*: Needles are embedded in the upper-jiao region, lower-jiao region, heart region, and spleen region on both sides of the eyes. At the same time, participants get rehabilitation training based on their major dysfunction.6.*Needles selection*: Specialized needles for eye-acupuncture combined with rehabilitation training therapy at the length of 0.30 mm × 8 mm, 0.25 mm × 8 mm, 0.30 mm × 7 mm, 0.25 mm × 7 mm (Patent Number: CN201320166807).7.*Position selection*: in the supine position.

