#### Secondary therapeutic outcomes

5.1.2

TCM syndrome score scale;WAB;Water swallow test;MoCA;GAP-43;MAP-2.

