#### Criterion of primary therapeutic outcomes

5.2.1

1.The comparison of obvious effective rate and effective rate in improvement degree of motor function and living ability among groups and within groups.2.The comparison of before-and-after treatment in fMRI of the brain in the resting state.

*Applying Nimodipine methods*:Clinical control rate: n ≥ 90%Obvious effective rate: 90% > n ≥ 70%Effective rate: 70% > n ≥ 30%Ineffective rate: n < 30%n = [(points before treatment − points after treatment) ÷ points before treatment] × 100%, n is expressed as a percentage.

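### The WAB and water swallow effective rates in Section 5.2.2 carry no baseline-deficit condition, so on the default reading unaffected participants dilute the group difference

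*Protocol article*

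**What the plan says.** Section 5.1.2 lists WAB and the water swallow test among the secondary outcomes: "TCM syndrome score scale;WAB;Water swallow test;MoCA;GAP-43;MAP-2". Section 5.2.2, item 3, sets the comparison of the obvious effective and effective rates "among groups and within groups made by ADL scales (modified Barthel index), WAB and water swallow test". It names no denominator, no analysis set and no rule for a normal baseline.

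The rate labels are defined only in Section 5.2.1, under the primary criterion. The measure there is "n = [(points before treatment − points after treatment) ÷ points before treatment] × 100" (a percentage). Obvious effective means at least 70% and below 90%, effective means at least 30% and below 70%, and the lowest band is "Ineffective rate: n < 30" (per cent). Section 5.2.2 gives its own cut-off (50%) for TCM symptoms but none for WAB or swallowing.

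Four other places bear on who is counted:

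- **Section 3.3:** the functional entry condition is "Modified Barthel index < 70, MRS ≥ 3". Speech and swallowing do not appear.
- **Section 4.1:** the regions for the speech component are needled "on both sides of the eyes for participants with speech disorder", so the authors expect some participants to have none.
- **Sections 5.4.1 to 5.4.3:** the primary and secondary scales are evaluated at each visit, without a deficit condition.
- **Section 2.9:** a full analysis set close to intention-to-treat, a per-protocol set and a safety set are defined, with no subset specific to an outcome.

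**The concern.** A responder rate based on percent improvement has meaning only for someone who can improve. Participants who speak and swallow normally at Visit 1 cannot respond. If they stay in the denominator, each arm's rate mixes two things: how many participants had the deficit, and how many of those responded. The first is a baseline feature that treatment cannot change.

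At stake is the sensitivity of two secondary outcomes. A real speech or swallowing benefit would appear as a small difference in low rates and could be reported as no effect.

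**Working it through.** **1. The plan's own figure.** Section 2.3 gives 80% vs 90%, one-sided α = 0.05, β = 0.20 and 157 per group. With pooled variance and no continuity correction:

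n = [1.645·√(2·0.85·0.15) + 0.842·√(0.80·0.20 + 0.90·0.10)]² / 0.10² = 156.6, so 157. Then 157/0.90 = 174.4, so 175.

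Both stated figures reproduce. They concern an overall effective rate, not WAB or swallowing, so they say nothing about the size of this problem.

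**2. How an unaffected participant is classified.** With an unchanged non-zero score, n = (b − b)/b = 0%, which is below 30% and so ineffective. If normal is scored 0, n = 0/0 and no band applies. The scoring of the two tests is not given, so either case is possible.

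**3. Effect on the difference.** Let f be the share with a deficit, and p₁ and p₂ the response rates among those affected. With everyone in the denominator and unaffected participants ineffective, the arms show f·p₁ and f·p₂. The difference is f·(p₂ − p₁), smaller than the true one for any f below 1.

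**4. Illustrative size.** The documents give neither f nor these rates. Assumed: f = 0.30, p₁ = 0.50, p₂ = 0.70.

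Rates over everyone: 0.30·0.50 = 15% and 0.30·0.70 = 21%, a 6-point difference in place of 20.

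Power = Φ{[Δ − z·√(2p̄(1−p̄)/n)] / √([p₁(1−p₁) + p₂(1−p₂)]/n)}, with the rates of the population analysed. At the plan's one-sided 0.05 (z = 1.645) and 180 per arm:

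- Everyone, n = 180: (0.06 − 1.645·0.0405)/0.0404 = −0.164, power 43.5%.
- Affected only, n = 0.30·180 = 54: (0.20 − 1.645·0.0943)/0.0923 = 0.487, power 68.7%.

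Other assumptions give the same direction:

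| Assumed response | Test, n per arm | f | Everyone | Affected only |
|---|---|---|---|---|
| 50% vs 70% | one-sided, 180 | 0.20 | 32% | 53% |
| 50% vs 70% | one-sided, 180 | 0.50 | 67% | 87% |
| 50% vs 70% | two-sided 0.05, 162 (10% dropout) | 0.20 | 20% | 37% |
| 50% vs 70% | two-sided 0.05, 162 | 0.30 | 29% | 52% |
| 50% vs 70% | two-sided 0.05, 162 | 0.50 | 50% | 74% |
| 80% vs 90% | one-sided, 180 | 0.20 | 13% | 32% |
| 80% vs 90% | one-sided, 180 | 0.30 | 16% | 42% |
| 80% vs 90% | one-sided, 180 | 0.80 | 49% | 77% |

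**5. Does the percent formula work for those who are affected?**

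- *WAB.* The formula credits only a fall in score. If higher is better (an assumption, since the direction is not stated), a rise from 40 to 80 gives (40 − 80)/40 = −100%, which is ineffective. Restricting the denominator would not repair that.
- *Water swallow.* If graded 1 to 5 with 1 normal (an assumption), full recovery from grades 2, 3, 4 and 5 gives 50%, 67%, 75% and 80%. The same end state therefore falls in different bands according to the starting grade. A one-grade gain from 5 to 4 gives 20% and counts as ineffective, while one from 3 to 2 gives 33% and counts as effective.

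**The case against.** The strongest reply is that the article does not say what population these rates use. It assigns no analysis set to them, the bands are written for the primary criterion, and Section 4.1 treats speech disorder as a subgroup, so a restricted WAB analysis fits the text. A condensed article may leave this to an analysis plan. That stands against any claim that the protocol orders all patients to be counted and scores the unaffected as failures. A reader might infer such a rule, but it is not written.

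What survives is narrower. Section 5.2.2 uses labels that have one definition in the document, the sets in Section 2.9 include no subset for these outcomes, and the visit schedule is unconditional. The default these produce is a poor one. Section 5.5 also says the trial has no blinding, so the population should be settled before results are seen.

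Four further inferences are tempting but not supported:

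- **A false benefit.** Under randomisation the shrinkage acts on both arms and moves the difference towards zero.
- **A top band out of reach for swallowing.** On the assumed grading no recovery reaches 90%, but Section 5.2.2 compares only the obvious effective and effective rates, and every full recovery falls in one of those.
- **The questionnaire screen removes aphasic patients.** The condition in Section 3.1 is "more than 80% completion without logical problem", and help in completing the form is allowed. Nothing shows how many it would exclude.
- **Counting participants who did not receive the speech component is itself an error.** That is ordinary intention-to-treat practice.

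**Conclusion.** The point holds in a limited form. Section 5.2.2 sets responder rates for two symptom-specific scales without a baseline-deficit condition, in a trial whose entry criteria do not require the symptom. The default reading dilutes the difference by the factor f.

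The direction follows from the formula, provided the Section 5.2.1 bands apply and unaffected participants are kept as ineffective. If a zero baseline made n undefined and those participants were dropped, the restriction would happen by accident of scoring. The size cannot be derived from the documents: 15% vs 21%, and power of 43.5% against 69%, rest on assumed values of f and of response. They also assume that the formula registers improvement among the affected, which fails for WAB if higher is better.

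The consequence is lost sensitivity on secondary outcomes that do not drive the sample size. It is worth correcting, but it does not threaten the primary analysis.

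**What to change.** In Section 5.2.2:

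1. Restrict the WAB and water swallow rates to participants with a deficit on that test at Visit 1, with the deficit threshold stated, and report that denominator by arm. Because the subset is defined at baseline, the comparison within it remains randomised.
2. Report new deficits among the other participants separately.
3. Define water swallow response as an improvement in grade (for example, return to normal) instead of percent change.
4. State the WAB scoring direction. If higher is better, reverse the sign of the formula or analyse change in score.

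The cost is wording only, since both tests are already scheduled at Visit 1 and no new data are needed. The downside is smaller denominators for these two outcomes. In every scenario computed above, the restricted comparison still had the higher power.

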### Discontinuation criteria

5.3

Discontinuation means that clinical trials have not been completed as planned and part of them have been stopped halfway. The purpose is to ensure the interests of the subjects, protect the quality of the trials, and avoid unnecessary economic losses.

The trial should be discontinued timely if serious safety problems happened.

The trial should be discontinued if the treatment is poor or ineffective, or with no clinical value in order to avoid delaying the effective treatment of the subjects and unnecessary economic loss;

The subject is not willing to continue the clinical trial and drops out halfway;

The subject with allergic reactions or other adverse reaction is supposed to drop out of the trial if researchers think it necessary.

Researchers should keep a record of the reasons subjects drop out in detail.

Automatic withdrawal (subjects who cannot insist on the treatment);Adverse events;Serious complication;Symptoms deteriorate and emergency measures must be taken.

### Measurement, records, time, and repetitions

5.4

The curative effect is assessed at baseline, 0, 2, and 4 weeks after each treatment and 4 weeks after the end of treatment during the follow-up period. Investigators will fill in the complete CRF forms and fax them to the clinical trial center and data management center in time.

Primary outcome measures: the first day of diagnosis, the 14th and the 28th day after treatment.

Secondary outcome measures: the first day of diagnosis, the 14th and the 28th day after treatment. The subjects are followed up for 4 weeks after treatment.

#### Visit 1 (Day-3∼0)

5.4.1

The basic demographic information, past medical and treatment history, course of the disease, complication, medication, and so on.General vital signs: temperature, respiration, heart rate, and blood pressure (measured after sitting still for 5 minutes).General physical examination and specialist examination.Laboratory examination: blood routine examination (red blood cell count, white blood cell count, platelet count, hemoglobin), urine routine examination, 4 coagulation tests (prothrombin time, activated partial thromboplastin time, plasma fibrinogen, and thrombin time), and 12-lead ECG examination.fMRI of the brain in the resting state and GAP-43 and MAP-2.Primary and secondary outcomes scale evaluation.Qualified patients (meeting all inclusion criteria and failing to meet all exclusion criteria) are randomly divided into groups based on the random number and they are informed of the treatment method.After the first treatment, the experimental group has an fMRI of the brain in the resting state.

#### Visit 2 (14th day after the treatment)

5.4.2

Keep a record of general vital signs: temperature, respiration, heart rate, and blood pressure (measured after sitting still for 5 minutes).General physical examination and specialist examination.Primary and secondary outcomes scale evaluation.Keep a record of adverse events and drug use.

#### Visit 4 (28th day after the treatment)

5.4.3

Keep a record of general vital signs: temperature, respiration, heart rate, and blood pressure (measured after sitting still for 5 minutes).General physical examination and specialist examination.Laboratory examination: blood routine examination (red blood cell count, white blood cell count, platelet count, hemoglobin), urine routine examination, 4 coagulation tests (prothrombin time, activated partial thromboplastin time, plasma fibrinogen, and thrombin time), and 12-lead ECG examination.fMRI of the brain in the resting state and GAP-43 and MAP-2.Primary and secondary outcomes scale evaluation.Keep a record of adverse events and drug use.

### Blinding test

5.5

No.

### Follow up

5.6

4-week follow-up by telephone after treatment. ADL scales (modified Barthel index).

## Safety and adverse events

6

### Indexes, time, and methods of safety

6.1

Blood routine examination (red blood cell count, white blood cell count, platelet count, hemoglobin), urine routine examination, 4 coagulation tests (prothrombin time, activated partial thromboplastin time, plasma fibrinogen, and thrombin time), and 12-lead ECG examination.

### Report form

6.2

All information about adverse events, whether mentioned by subjects, found by investigators, or assessed by physical examination, laboratory examination or other methods, should be recorded on the case report form.

### Breaking blinding and treatment in emergency

6.3

When serious adverse events happen, researchers should break blindness and take symptomatic treatment immediately.

### The definition of serious and non-serious adverse events

6.4

#### Adverse events

6.4.1

Adverse events cover all the occurrence of deterioration of symptoms and syndrome. It also includes relevant clinical conditions found in the laboratory or any process of diagnoses, such as unscheduled treatment measures, withdrawal from the trial, or the abnormal laboratory examination items exceeding the norm for 20%. Adverse events may include new disease, deterioration of symptoms or signs during treatment, the effect of drugs, unrelated to participation in the trial, and a combination of 1 or more factors. Therefore, the term adverse event does not mean causality with the intervention.

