### Cases of dropouts

2.7

1.When participants drop out of the study, researchers should try to contact them, ask for reasons, record the last time of medication, and finish the evaluation items.2.When participants drop out because of adverse events, researchers should take appropriate treatment and closely follow them up until the adverse events disappear or recover. Adverse events should be recorded and filled out in a case report form (CRF) and carried out statistical analysis.3.Researchers should record the main reasons for dropout.4.Whether participants drop out or not, all that have been recruited and have used the treatment number should be kept as records, which can be analyzed by intention-to-treat (ITT) analysis. There is no need to add cases after dropouts and all CRFs should be submitted to the statistical unit to make the analysis. The dropout rate of this clinical study should be under 10 percent.

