#### Criteria for adverse reactions

6.5.2

1.*Definitely related*: The occurrence of the reaction conforms to the reasonable time sequence after medication and the known reaction type of the suspected treatment method. The reaction is improved after discontinuation but reappears after treatment again.2.*Probably related*: The occurrence of the reaction conforms to the reasonable time sequence after medication and the known reaction type of the suspected treatment method. The patient's clinical state or other treatment methods may also lead to the same reaction.3.*Probably not related*: The occurrence of the reaction is not quite consistent with the reasonable time sequence after medication and the known reaction type of the suspected treatment method. The patient's clinical state or other treatment methods may also lead to the same reaction.4.*Definitely not related*: The occurrence of the reaction does not meet the reasonable time sequence after medication and some of the reactions cannot be explained by the treatment in the trials. The reaction may take place because of the patient's clinical state or other treatment methods, disappear when the state improves or treatment ends and reappear when using other methods repeatedly.5.*Unknown*: The occurrence of the reaction does not have a definite relation with the time sequence after medication. Both the suspected and other treatments in the trial can lead to the reaction.

The definitely related, the probably related and the unknown can be regarded as adverse reactions of the treatment.

During the trial, researchers are required to observe and fill in the time, severity, duration, measures, and outcomes of any adverse events carefully and to follow up properly. If an abnormal value with clinical significance is found, it should be observed at least once a week until it reaches the normal or baseline level.

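### Section 6.4.1 names trial withdrawal as an adverse event without limiting it to medical causes, and its 20% laboratory criterion has no Visit 1 reference and no clear direction

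*Protocol article*

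**What the plan says.** Section 6.4.1 of the protocol article defines adverse events in two steps. The first is worsening: "Adverse events cover all the occurrence of deterioration of symptoms and syndrome". The second is an addition: "It also includes relevant clinical conditions found in the laboratory or any process of diagnoses", followed by the examples "such as unscheduled treatment measures, withdrawal from the trial, or the abnormal laboratory examination items exceeding the norm for 20" percent.

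Other sections bear on how this is applied:

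- Section 2.7 makes an adverse event one possible cause of dropout: "When participants drop out because of adverse events, researchers should take appropriate treatment". It also asks for the main reason for every dropout, sends adverse events to statistical analysis and sets a dropout rate below 10%.
- Section 5.3 lists the reasons for dropout as separate entries: "Automatic withdrawal (subjects who cannot insist on the treatment);Adverse events;Serious complication", followed by deterioration that needs emergency measures.
- Section 6.1 names the safety tests: "Blood routine examination (red blood cell count, white blood cell count, platelet count, hemoglobin), urine routine examination, 4 coagulation tests", and an ECG. Sections 5.4.1 and 5.4.3 take them at Visit 1 and at the day-28 visit, labelled Visit 4.
- Section 6.2 requires everything on adverse events to be recorded: "All information about adverse events, whether mentioned by subjects, found by investigators, or assessed by physical examination, laboratory examination or other methods".
- Section 6.5.2 says of a clinically significant abnormal value that "it should be observed at least once a week until it reaches the normal or baseline level".

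**The concern.** An adverse-event definition is a counting rule, and six centres will apply this one. Two parts of it can produce counts that do not reflect harm.

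First, a patient who no longer wishes to take part has withdrawn. Under section 6.4.1 as written that can be coded as an adverse event, while under section 5.3 it is a dropout for a reason other than an adverse event. Once coded as an event, it needs a severity, a duration, an outcome and a five-level causality grade (section 6.5), none of which fits a change of mind. If the causality is graded as unknown, section 6.5.2 then classes it as a reaction to the treatment.

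Second, a laboratory value outside the range before treatment and unchanged after it says nothing about treatment, yet it meets a criterion that looks only at the norm.

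What is at stake is the safety comparison. Section 5.5 states that there is no blinding, so patients may leave one arm more often for reasons unrelated to harm. A difference in withdrawal could then appear as a difference in safety. Unchanged abnormalities would add events to both arms that carry no information about treatment.

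**Working it through.** **1. The plan's own figures.** The 10% dropout comes from the sample-size paragraph (section 2.3): 80% v 90%, one-sided α = 0.05, β = 0.20. With the pooled-variance formula for two proportions, mean proportion 0.85:

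n = [1.645 × √(2 × 0.85 × 0.15) + 0.842 × √(0.80 × 0.20 + 0.90 × 0.10)]² / 0.10² = 156.6, so 157 per group.

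157 / (1 − 0.10) = 174.4, so 175.

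Both agree with the plan. The present point does not depend on them. They only confirm the 10% and the 180 per group used below.

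**2. Withdrawal: the sections side by side.** The four reasons in section 5.3 can be read against section 6.4.1.

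| Reason in 5.3 | Adverse event by the worsening limb of 6.4.1? | Adverse event by the withdrawal example? |
|---|---|---|
| Own withdrawal | Only if a medical event lies behind it | Yes, read literally |
| Adverse event | Yes | Yes |
| Serious complication | Yes | Yes |
| Deterioration needing emergency measures | Yes | Yes |

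The withdrawal example adds nothing for the last three reasons, which already count. Its only effect is on the first, which section 5.3 separates from adverse events.

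**3. Size of the withdrawal effect.** 0.10 × 360 = 36 patients, or 0.10 × 180 = 18 per arm. Section 2.7 asks for a rate strictly below 10%, so about 36 is the upper end. The documents do not give the share without a medical cause, so the added count runs from 0 to about 36.

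**4. Illustration only.** Let p be the true adverse-event proportion and w the proportion withdrawing without a medical cause, taken as independent. The counted proportion is 1 − (1 − p)(1 − w). All values of p and w here are assumptions.

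| p | w | Counted |
|---|---|---|
| 5% | 5% | 1 − 0.95 × 0.95 = 9.75% |
| 5% | 10% | 1 − 0.95 × 0.90 = 14.5% |
| 10% | 5% | 1 − 0.90 × 0.95 = 14.5% |
| 10% | 10% | 1 − 0.90 × 0.90 = 19.0% |

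With p = 5% in both arms and w = 13% in one and 7% in the other (10% overall), the counts are 1 − 0.95 × 0.87 = 17.35% and 1 − 0.95 × 0.93 = 11.65%. That is a difference of 5.7 points with no difference in harm. If w is equal in both arms, the effect is dilution: true proportions of 5% v 10% with w = 10% become 14.5% v 19.0%, and the ratio falls from 2.0 to 1.31.

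**5. Laboratory criterion.** Take a value 25% outside the range at Visit 1 and again at Visit 4. The change is zero, but 25% is more than 20%, so the criterion is met. The worsening limb does not prevent this, because the laboratory clause is written as an addition to it. The documents give no frequency of such values. An assumed 1% to 10% of participants would be 0.01 × 360 = 3.6 (about 4) to 0.10 × 360 = 36. A baseline level appears only in section 6.5.2, as an end point of follow-up, and not in the definition.

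**6. Direction.** The criterion can be read as more than 20% above the upper limit, or as more than 20% outside the range on either side. The text does not decide between them. It matters because the tests include platelets, hemoglobin and fibrinogen, for which a fall can be the relevant change.

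**The case against.** The best defence is the phrase that governs the list. The examples illustrate relevant clinical conditions found by laboratory or diagnostic work, and someone who merely declines to continue has no such condition. Sections 2.7 and 5.3 then show how the clause is meant to be applied. This softens the point but does not remove it. Withdrawal is itself given as an example of such a condition, with no limit on cause, and a centre coding from section 6.4.1 has no instruction to leave it out.

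On baseline values, the laboratory items must be abnormal and relevant, candidates are screened on examination indicators (section 3.1) and bleeding tendency is excluded (section 3.4). Marked abnormalities at entry should therefore be fewer. That limits the number but does not supply the missing reference. Rules for treatment-emergent events are often left to an analysis plan, but here the protocol states a rule, and the stated rule is what gives the wrong count.

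It is also fair that dropout reasons and both sets of laboratory values are collected, so the miscounts can be separated later, and that the article specifies no between-arm test of adverse events.

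A reader might go further and infer that harmful falls are not counted, or that the rule misses the laboratory changes most relevant to bleeding. The documents do not support either. The wording can mean outside the range on either side, and the list is illustrative. Sections 6.2 and 6.5.2 cover laboratory findings and clinically significant abnormal values whatever their direction. Three of the four coagulation tests (prothrombin time, activated partial thromboplastin time, thrombin time) signal bleeding risk when they are prolonged, so even an upward-only reading would catch them.

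**Conclusion.** The point holds as a defect in a stated rule. Section 6.4.1 names withdrawal as an adverse event whatever its cause, against sections 2.7 and 5.3. Its 20% criterion has neither a Visit 1 reference nor a clear direction.

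Through withdrawal alone, between 0 and about 36 of 360 patients could be added to the adverse-event count. The upper end requires dropout at the full 10% with no medical cause in any case. It would be wrong to conclude that the trial's adverse-event rate will be inflated by a particular factor. The event rates, the non-medical share and the split by arm in the illustration are assumptions, and none is in the documents.

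The consequence is confined to adverse-event counts in the safety analysis. Sample size and efficacy analysis are untouched. Because the remedy uses data already planned, the correction is worth making.

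**What to change.** In section 6.4.1:

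- Remove withdrawal as an adverse event in its own right. Count the medical event that led to it, if there was one, and report withdrawals in a separate table by the reasons in section 5.3. A patient's own withdrawal should prompt a question about a medical cause, since being unable to continue treatment may have one.
- Keep the protocol's 20% margin, state that it applies outside the normal range in either direction, and count only values that are new or worsened relative to Visit 1.

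The cost is the rewording, a matching CRF instruction so that all centres code alike, and a shift table from Visit 1 in the safety output. No new data are needed: the Visit 1 and day-28 laboratory values and the dropout reasons are already collected.
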